**Figure 1 figure1:**
[figure not shown]
The engAGE platform. engAGE: Managing Cognitive Decline Through Theatre Therapy, Artificial Intelligence, and Social Robot–Driven Interventions; ML: machine learning.

#### The Social Robot Service

As the social robot service, the Android version of Pepper’s tablet offers dashboards for cognitive games, storytelling, and activities to the end user through an easy-to-use interface. Equivalent cognitive games are also integrated into the communication service to allow the end user to play them on the tablet at home. Pepper is a humanoid social robot able to dialogue with the user by speaking, moving, and expressing emotions, being also equipped with an Android tablet placed at its chest. The user logs through the tablet at every session and then interacts with the robot and plays the planned activities (drama play or cognitive games). To track the user’s progress, each performance is recorded, and scores are sent to the cloud, along with the user ID. As the sessions are held in groups of 4 or 5 older adults, the users can choose to play individually or in teams. Once the type of game is selected, the user is redirected to a new screen in which all the games corresponding to the type selected is displayed. When the user plays and succeeds in a task, the robot congratulates them. To ensure that the user understands the robot, the words the robots says are displayed on the screen like subtitles. The interaction is recommended to be vocal as much as possible to improve the user experience. Different categories of cognitive games and storytelling activities are implemented in the service. The games are and will be iteratively developed and included in the service in the different versions of the prototype while considering end users’ feedback:

Familiar games: crosswords, memory cards, and remembering objects that appearQuizzes: picture, musical, and cultural quizzesStory-/play-telling: story listening, poem recitation, and YouTube shorts, with questions asked about the activity

#### The Communication Service

The communication service is the hub of the entire system for providing dashboards for end-user interactions at home. It is a web app with several dashboards through which all the end users’ categories can communicate. This service is based on the MEMAS Life Mastering Assistant with the following functionalities that helps people with MCI: a calendar with reminders, step-by-step instructions for daily activities in the form of a series of images with spoken comments or videos, easy-to-access radio channels via streaming, photos with spoken comments and videos, music, easy-to-access network newspapers, cognitive games, weather forecasts, self-reporting questioners, and graphical results from the ML algorithms for secondary end users. The service is usable by both primary and secondary users. The primary user can be connected to several secondary users. In the administration module (a website page), the secondary user (ie, family member or formal caregiver) can manage an activity calendar, build albums with photos and videos, and configure access to favorite radio channels and newspapers. In general, the secondary user can edit the primary user’s interface to make using the service as simple as possible and tailored to the primary user’s needs. Data regarding self-assessment and cognitive games scores are sent to the ML service for further analysis. In this service also, the games are and will be iteratively developed and included in the service in different versions of the prototype while considering end users’ feedback: Sudoku, Mahjong, Minefield, crosswords, logics, math, Hangman, and memory cards.

#### The Monitoring Service

The monitoring service offers a tablet-based app where parameters such as the heart rate, sleep status, and physical activity (steps and distance walked) are monitored. These data are further used by the ML service as input for its algorithms. The monitoring service has little user interaction outside of the use of sensor devices. This service features a mobile app gateway that transfers data from the sensor device (Fitbit) into the cloud. In the first iteration, it transfers Fitbit data from the Fitbit service. It does so automatically while running in the background on the mobile device (Android tablet) of the primary user. Once the login and Fitbit authentication have been established, the app runs in the background, regularly polling data from the Fitbit service.

#### The ML Analytics Service

The ML analytics service has no direct end-user interaction; it gets data from the monitoring service and the communication platform and provides results to be displayed in the latter. The main goal of the service is to assess and correlate the daily physical activity, sleep parameters, game scores, and self-assessment data to offer a view of MCI progress [21]. It combines deep neural network algorithms/models to analyze objective activity data coming from the Fitbit wearable, with graph learning techniques that capture structural insights from subjective self-reporting activities to construct a better understanding of symptoms associated with cognitive decline.

### Study Design

The PoC was structured as a controlled longitudinal pilot study, with a before-and-after design, where observations were run on a series of enrolled individuals, who received the intervention described later, with data collected before and after the installation and use of the technical solution. The goal of trial evaluation was to demonstrate the viability of engAGE technology integration into everyday life to counteract cognitive decline. As secondary outcomes, the impact on the social dimension and quality of life of end users was evaluated. Moreover, acceptance over 6 months and the usability of proposed solutions were evaluated to understand the feasibility of the intervention. Despite the choice to structure the PoC as an RCT in order to provide more robust evidence on feasibility and efficacy [22,23], a formal sample size calculation was not performed. Practical constraints within the project were considered while deciding the number of end users to enroll. In fact, recruitment timelines, availability of rooms and professionals, and technical equipment represented practical limits for the study feasibility. After considering these constraints, the sample size for the PoC was set to 80 primary end users: 50 (62.5%) in the experimental group (EG) and 30 (37.5%) in the control group (CG).

In Italy, end users were recruited from the Neurology Unit and Alzheimer Assessment Unit (Memory Clinic) and from the Alzheimer daycare center of the Istituto di Ricovero e Cura a Carattere Scientifico – Istituto Nazionale di Riposo e Cura per Anziani (IRCCS INRCA). The research team could communicate with potential participants of previous projects and initiatives, as well as with other people who might have been be interested in contributing to the project evaluations. This method made it possible to be in contact with clients met before and with whom a relationship of trust was already established.

In Norway, participants were recruited from two daycare and housing centers in the city of Arendal. The first one, Solhaug, is a daycare center for old residents living in their own homes, while the second one, Plankemyra, is a combined housing and daycare center.

In Switzerland, end users were recruited with the help of a home assistance and care institution, the Geneva Institution for Homecare and Assistance (IMAD). The research team also reached the partner patient program for participants with potential MCI. All older adults interested in the study were considered for participation.

#### The Experimental Group

The EG used the engAGE system in two different settings: at health care organizations and at home. For the Italian site, the health care organizations were the Neurology Unit and Alzheimer Assessment Unit (Memory Clinic) and the Alzheimer daycare center of the IRCCS INRCA. Weekly sessions were run at the IRCCS INRCA usability lab (YOUSE) in the hospital. For the Norwegian site, weekly sessions were managed at Solhaug and Plankemyra in the city of Arendal. For the Swiss site, the participants (primary end users) attended weekly sessions at the Hôpitaux Universitaires de Genève’s (HUG) living lab. At the health care organizations, the primary end users interacted with Pepper. The interaction was supervised by tertiary end users (formal caregivers, ie, occupational therapists, psychologists, or psychotherapists) and included the following activities: dialoguing with the robot, storytelling, drama play, and cognitive and physical games. The human-robot interaction was planned to last about 1 hour and to be scheduled once a week for 6 months. At home, the older adults interacted with the tablet, supervised by informal caregivers (relatives). In addition, the primary end users played cognitive and physical games installed on the MEMAS app. This activity was suggested to be performed for 30 minutes every day for 6 months. Throughout the entire period of experimentation (unless they decided otherwise), the older adults wore the smartwatch for measuring their physiological parameters and steps. Any activity performed by them was assigned by formal caregivers and could be personalized, considering the primary end users’ abilities (difficulty levels of the games), lifestyle (reminding and monitoring services), and social interactions. Before starting the PoC, one session was dedicated to primary end users to teach them how to use the activity tracker and the MEMAS app at home. During weekly sessions, they were allowed to ask for clarifications about the use of these devices, and they could receive remote support from technicians during the week if any problem occurred.

Figure 2 shows the scheme of the intervention for the EG.

**Figure 2 figure2:**
[figure not shown]
EG study design. EG: experimental group..

#### The Control Group

Participants assigned to the CG received a booklet in which cognitive games were illustrated. Moreover, suggestions on how to live a healthy life with active aging were provided in the booklet. At the beginning of the trial, the participants in the CG were invited to follow the booklet, play the cognitive games, and follow the suggestions, but they were neither motivated nor contacted during the experiment, unless they wished otherwise.

### The RCT Phases

The PoC procedure was divided into three different phases after recruitment of the participants: baseline evaluation (T0), midterm evaluation (T1; after 3 months from T0), and final evaluation (T2; after 6 months from T0); the aim was to collect data, as described in Textbox 1. All questionnaires and scales at each phase of the PoC were administered through face-to-face interviews by eligible professionals at health care facilities.

Proof-of-concept (PoC) phases.
**Recruitment phase:**
The recruitment protocol included general information about the subjects, in particular their health status and cognitive condition. The information was collected with the help of the caregivers/family members, if needed.
**Baseline evaluation:**
This phase consisted of the first real contact with the users and their families before the start of the PoC.
**Second evaluation (after 3 months of use):**
The aim of the midterm evaluation was to collect useful information about the use of the engAGE (Managing Cognitive Decline Through Theatre Therapy, Artificial Intelligence, and Social Robot–Driven) platform after a short period of use for detecting and analyzing technology acceptance and usability issues. Obviously, the control group (CG) was not evaluated at this stage.
**Final evaluation (after 6 months of use):**
The aim of this phase was to collect useful information about the benefits perceived by the users after a meaningful period of use of the engAGE system. The final evaluation was conducted after system deinstallation in order to detect and analyze the impact of the system on the daily life of older adults and their families.

### Recruitment

A specific number of people were recruited for the study via health care institutions or health care organizations. Potential participants were evaluated by eligible professionals through face-to-face interviews to verify that eligibility criteria were met. Those who did not meet the criteria or declined participation were excluded. The remaining participants were randomly assigned to the EG or the CG. A randomization technique, conducted by a statistician, based on a single sequence of random assignments was adopted. A list of random numbers was generated by the computer, while subjects were assigned a number based on their order of inclusion in the study. According to this technique, in Italy and Switzerland, the 30 subjects were randomly assigned to one of the two study groups (n=20, 66.7%, in the EG and n=10, 33.3%, in the CG), while in Norway, 20 subjects were equally assigned to the two groups. Next, for both groups, we took careful note of who were lost to follow-up, who discontinued intervention, or who were excluded from analysis. The procedure adopted is summarized in Figure 3.

**Figure 3 figure3:**
[figure not shown]
Recruitment methodology flowchart. CG: control group; CH: Switzerland; EG: experimental group; IT: Italy; NO: Norway.

### Older Adults With MCI

Once informed consent was obtained in duplicate, compliance with the inclusion and exclusion criteria of the study (Textbox 2) were verified, and baseline evaluation was carried out using questionnaires.

Inclusion and exclusion criteria for people with mild cognitive impairment (MCI).
**Inclusion criteria:**
Aged ≥65 yearsCapacity to provide informed consentAlready diagnosed with MCIGlobal Deterioration Scale (GDS) [24] score<1Montreal Cognitive Assessment (MoCA) score [25] between 21 and 25Memory Assessment Clinic Questionnaire (MAC-Q) [26] score≥25Reisberg scale [27] score between 2 and 4Clinical Frailty Scale [28] score between 1 and 3Having an informal/formal caregiver to support in carrying out the main daily activities
**Exclusion criteria:**
Failure to meet inclusion criteriaConcomitant participation in other studiesLack of written informed consentSignificant visual or hearing impairment

#### Informal Caregivers

Informal caregivers are mostly family members or daily references of patients. Connections between informal caregivers and clients are private and not via a health care organization. Informal caregivers are concerned about the well-being of patients, and they provide emotional or practical support regularly. Although it is easier to live near the patients, informal caregivers do not necessarily need to live close by. Informal caregivers were included in the engAGE project since they play an important role in the daily life of people with MCI (Textbox 3). Moreover, informal caregivers can fulfil caring tasks to reduce the burden of formal caregivers. A good collaboration between informal and formal caregivers is needed as informal caregivers can be the link between client and formal caregiver.

Inclusion and exclusion criteria for informal caregivers.
**Inclusion criteria:**
Being the informal caregiver of an older adult with mild cognitive impairment (MCI)Availability of time to participateVisiting the patient at least two times a week or living with them
**Exclusion criteria:**
Failure to meet the inclusion criteriaConcomitant participation in other studiesLack of written informed consent

#### Formal Caregivers

Care professionals or formal caregivers are professionally responsible for dementia care. They are trusted agents for people with MCI and have direct contact with older adults and provide care when needed.

Formal caregivers are case managers, neurologists, psychotherapists, occupational therapists, and nurses. The case manager was responsible for the organization. The neurologist was a specialized medical doctor who diagnosed the disease and prescribed treatment. The psychotherapist led the intervention, whereas the nurses and occupation therapists acted as assistants. These professionals might be especially found in daycare, but they are available in residential home care as well (Textbox 4).

Inclusion and exclusion criteria for formal caregivers.
**Inclusion criteria:**
Over 1-year experiencePsychologist, neurologist, occupational therapist, or nurse from a health care facility or paid by the participantsAvailability of time to participate
**Exclusion criteria:**
Failure to meet the inclusion criteriaConcomitant participation in other studiesLack of written informed consent

### Outcomes

The PoC aimed to assess the feasibility of using the engAGE platform as a support tool to counteract cognitive decline in older adults with MCI. For this reason, the primary interest was to assess the impact of the engAGE platform on cognitive capacity. Secondarily, the study also focused on the impact on the social dimension and quality of life, as well as the usability and acceptability of the platform. All the outcomes are presented in Table 1.

**Table 1 table1:** Tools and dimensions of the primary end users’ protocol.

Outcome	Clinical assessment
Perceived stability of cognitive status by older adults	MAC-Q^a^ [26]
Acceptability of the engAGE^b^ platform	UTAUT^c^ [29]
Social connectedness of older adults	UCLA^d^ [30]
Reduction in the caregiver burden of formal and informal carers	Zarit et al [31]
Adherence to intervention	Ad hoc questionnaire
Well-being of informal caregivers	WEMWBS^e^ [32]
Quality of life of older adults	EuroQol 5-Dimension 5-Level (EQ-5D-5L) [33], Quality of Life-Alzheimer’s Disease (QoL-AD) scale [34]
Usability and affordability of the solution of informal caregiver	SUS^f^ [35]
Improving the quality of work of formal carers	Ad hoc questionnaire

^a^MAC-Q: Memory Assessment Clinic Questionnaire.

^b^engAGE: Managing Cognitive Decline Through Theatre Therapy, Artificial Intelligence, and Social Robot–Driven Interventions.

^c^UTAUT: Unified Theory of Acceptance and Use of Technology.

^d^UCLA: University of California, Los Angeles.

^e^WEMWBS: Warwick-Edinburgh Mental Well-Being Scale.

^f^SUS: System Usability Scale.

### Data Analysis

This subsection describes the measurements, statistical tests, and tools with which the data collected in the engAGE PoC were, and are still being, analyzed. The different types of data that were collected in the engAGE project are as follows:

Credentials: username, password, email address, and similar security information used for authentication and account access in different services of the platformPersonal data: first name, last name, gender, age, weight, height, email address, contact address, and phone number of older adults in different services of the platformAnswers to specific questions in self-assessment questionnaires on MEMASGames score from Pepper appsMeasurements and monitored parameters: weight, heart rate, blood pressure, and physical activities gathered through the monitoring infrastructureHistorical data of the measurements and monitored parameters for training and using ML algorithms for each older adult in the ML service

In the engAGE testing and evaluation phase, the following data were, and are being, processed:

Information and results from questionnairesCognitive game scoresHistorical data of measurements collected for each end userAny information the end users decided to share through discussions/interviews, as well as data providing feedback from trialsOutcomes that concern feasibility (ie, the primary interest of the engAGE PoC): recruitment rate (proportion of eligible individuals who consent to participate in the study, ie, those who attended more than 80% of weekly sessions), retention rate (proportion of participants who completed the 6-month intervention period), and adherence to the intervention (average number of interactions with the Pepper robot during weekly sessions, the frequency of use of the MEMAS app, and the activity tracker recording time)

Descriptive statistics (means, SDs, medians, IQRs) will be used to summarize adherence metrics.

Outcomes that concern efficacy of the engAGE intervention were considered exploratory and dealt with the metrics about cognitive capacity, quality of life, social dimension, and stress and care load relief (for caregivers). In particular, to explore the potential efficacy, changes in these domains before and after the intervention were analyzed. Paired *t* tests (for normally distributed data) or Wilcoxon signed-rank tests (for nonnormally distributed data) were used to compare pre- and postintervention scores within each group, while independent samples *t* tests or Mann-Whitney U tests were performed to assess between-group differences in change scores. Moreover, effect sizes (Cohen d or Cliff δ) were calculated to quantify the magnitude of any observed differences. Due to the nature of the PoC, this study was not powered to detect statistical significance. *P* values will be reported without adjustments for multiple comparisons and interpreted with caution. All analyses were planned for descriptive purposes, and only participants with at least 80% of adherence to the intervention were considered for analysis.

The aforementioned analyses were also applied to acceptance and usability measurements (ie, UTAUT and SUS scores) that provided insights into the primary goal of the study: the feasibility of the intervention. Data from the ML service were analyzed to correlate physical activity, sleep parameters, game scores, and self-assessment data. Longitudinal data analysis techniques (eg, mixed effects models) were used to analyze changes in these parameters over time and assess potential correlations with cognitive and quality-of-life outcomes.

The first step in the data analysis dealt with the description of the sample. Continuous variables will be reported as either the mean (SD) or the median (IQR) on the basis of their distribution (assessed using the Kolmogorov-Smirnov test). Categorical variables will be expressed as an absolute number and percentage. Mann-Whitney U tests (for nonnormal distribution) or chi-square tests (for normal or nonnormal distribution) were used to compare independent and dependent variables between the pre- and postintervention conditions, in addition to simple descriptive statistics (means, medians, and SDs, as appropriate).

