## Results

Recruitment started in October 2023 and continued until April 2024, when there was still time to attend 80% of the trial in the three sites. At the end of recruitment, 40 (81.6%) of the total 49 older adults with MCI were assigned to the EG and 9 (18.4%) to the CG. The PoC started in November 2023 and ended in July 2024. The start and end dates were different across countries because of the various difficulties encountered in organizing the trial and recruiting end users in each site. The efficacy of the engAGE platform will be demonstrated on the basis of the improvement or maintenance of cognitive capacity. In addition, the effects on the quality of life and social connectedness of primary end users, as well as the reduction in the care load and stress of caregivers, will contribute to determining the importance of the platform. Furthermore, the feasibility of the engAGE intervention will be assessed on the basis of the usability and acceptance of the platform, both measured through standardized quantitative scales. Data analysis was completed at the end of 2024, and the results will be published at least by 2026.

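### The recruitment rate cannot be relied on to measure uptake: the sections disagree on whether eligibility precedes consent, and its numerator is glossed as session attendance

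*Protocol article*

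**What the plan says.** All references are to the protocol article.

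- **Data Analysis** lists three feasibility outcomes and calls feasibility the primary interest of the proof of concept. The first outcome is the "recruitment rate (proportion of eligible individuals who consent to participate in the study". The same parenthesis continues: "ie, those who attended more than 80% of weekly sessions". Retention and adherence follow as separate outcomes.
- **Older Adults With MCI** puts consent before the eligibility check: "Once informed consent was obtained in duplicate, compliance with the inclusion and exclusion criteria of the study (Textbox 2) were verified".
- **Textbox 2** lists absence of written consent among the exclusion criteria for people with MCI.
- **Recruitment** describes the process differently: "Potential participants were evaluated by eligible professionals through face-to-face interviews to verify that eligibility criteria were met". It then says: "Those who did not meet the criteria or declined participation were excluded".
- **The Control Group** describes a booklet given at the start. After that, "they were neither motivated nor contacted during the experiment, unless they wished otherwise".
- **Results** reports that "40 (81.6%) of the total 49 older adults with MCI were assigned to the EG and 9 (18.4%) to the CG". The target under Study Design was 80.
- **Safety and Security Considerations** says that screening data were discarded once the project was complete.

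**The concern.** A recruitment rate in a feasibility study should show what share of suitable people agree to take part. That requires suitable people who refused to be in the denominator, and agreement, not later behaviour, to be in the numerator. The definition secures neither.

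If eligibility is settled only after consent, and lack of consent itself makes a person ineligible, refusers never reach the denominator. If eligibility is judged first and refusal is recorded separately, they do. The article supports both and does not say which applies to this rate. The attendance gloss then replaces agreement with adherence, which the same list already covers as its own outcome.

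Uptake matters here. Enrolment reached 49 of 80, Results mentions difficulties in recruiting, and Limitations wants the findings to inform the sample size and conduct of later studies. A reader given a single percentage could not tell whether it reflects refusals, poor attendance or neither.

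**Working it through.** **Inputs.** Enrolled and assigned: 49, of whom 40 are in the experimental group (EG) and 9 in the control group (CG), from Results. The article gives neither the number of eligible people who declined (D) nor the number of EG members above the attendance threshold (A). Both are assumptions, shown as ranges. No alpha, power or effect size enters, and Study Design states that "a formal sample size calculation was not performed".

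**Step 1: the article's own figures.** The article states no recruitment rate, so only the split can be reproduced. 40 + 9 = 49; 40/49 = 81.6%; 9/49 = 18.4%. These agree with Results.

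**Step 2: who can be eligible.**

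| Section | Order | Can an eligible person have declined? |
|---|---|---|
| Older Adults With MCI, with Textbox 2 | Consent, then criteria; no written consent means excluded | No |
| Recruitment | Interview against criteria; refusal is a separate reason for exclusion | Yes |

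**Step 3: the rate under each reading.** The 49 assigned are taken as the people who were both eligible and consenting.

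(a) Numerator consent, eligibility following consent: rate = 49/49 = 100%. Refusals cannot change it.

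(b) Numerator attendance, same denominator, CG included: rate = A/49. No weekly sessions are described for the CG, so A is at most 40.

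| A | Share of the 40 EG members | A/49 |
|---|---|---|
| 40 | 100% | 81.6% |
| 32 | 80% | 65.3% |
| 24 | 60% | 49.0% |
| 20 | 50% | 40.8% |

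(c) Numerator consent, eligibility preceding consent (Recruitment): rate = 49/(49 + D).

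| D | 49/(49 + D) |
|---|---|
| 0 | 100% |
| 5 | 90.7% |
| 10 | 83.1% |
| 25 | 66.2% |
| 49 | 50.0% |

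**Step 4: comparison.** A result near 66% could mean that 32 EG members attended enough sessions, with refusals ignored (65.3%), or that 25 eligible people refused, with attendance ignored (66.2%). The definition does not say which. Only (c) measures uptake. In (b) the rate moves, but decliners are still absent.

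**The case against.** Recruitment is the section that governs enrolment, and it supports a sensible denominator. The exclusion for lack of written consent is a stock line, repeated in the caregiver textboxes beside an equally formulaic line about failing the inclusion criteria. A phrase about eligible people who consent makes most sense if eligibility means the clinical criteria. The recruitment flowchart is not shown and might settle the order. The Outcomes section and the primary endpoint named in Data Analysis point to cognition, so this rate is not the trial's single main outcome.

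Much of this stands. Recruitment offers the more natural reading, and the rate is one of three feasibility outcomes. It does not remove the contradiction. Older Adults With MCI states the opposite order in plain terms, and even without the stock exclusion line, people who refuse before the check would never have their eligibility verified. Nor does it rescue the attendance gloss.

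Three stronger inferences are tempting and should not be drawn:

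- **That the rate is 100% whatever happens.** This is true only under reading (a). The full wording brings in attendance, and Recruitment allows decliners in the denominator.
- **That a later trial would understate the pool it needs by a known factor.** Any such factor is the reciprocal of an assumed uptake (1/0.7 = 1.4, 1/0.3 = 3.3). The article gives no count of refusals.
- **That the definition conceals the shortfall.** Results states 49 enrolled and mentions the difficulties, and a consent proportion alone would not explain them.

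**Conclusion.** The point holds as a defect of definition in a named feasibility outcome. The denominator is contradictory between Recruitment on one side and Older Adults With MCI with Textbox 2 on the other. The numerator mixes consent with an adherence threshold that does not apply to the control group as described.

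For the same 49 people, the possible results are a fixed 100%, at most 81.6%, or anything from 100% down to 50.0% over the assumed range of 0 to 49 decliners. As fully worded, and with eligibility following consent, the rate varies with attendance but still leaves out everyone who refused. Deleting the attendance gloss alone would not be enough, because on that order it would leave the uninformative 100%.

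The 81.6% ceiling assumes that controls stay in the denominator and have no weekly sessions. The decliner and attender counts are illustrations, not estimates.

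**What to change.** 1. In Data Analysis, define the denominator as people who meet the clinical criteria of Textbox 2, judged before and regardless of consent. The exclusion for lack of written consent plays no part in this denominator. Where decliners were not assessed, use people approached and say so.
2. Define the numerator as those who gave written consent.
3. Report attendance above 80% under adherence, for the experimental group.
4. Reconcile the order of consent and eligibility check between Recruitment and Older Adults With MCI.
5. Report the numbers approached, clinically eligible, consented and assigned, by country.

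The rewording is cheap, and the results are described as still to be published. The counts may be harder to obtain, since the article says screening data were discarded on project completion. If they no longer exist, the report should state that uptake cannot be estimated and should give no rate on a consented-only denominator. The cost is that the reported rate may be less favourable, or not estimable at all.
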